#### Statistical Analysis Plan

Feasibility will be assessed using proportions and exact binomial CIs. Acceptability will be evaluated using a random-effects model with a participant-specific random effect to account for within-participant correlation among ratings. This model will also facilitate estimation of the between- and within-participant variance of the ratings. Qualitative exit interviews will be coded by 2 independent coders with a goal of interrater reliability >0.80. Discrepancies will be resolved by consensus, and themes will be derived from iterative review of coded data. To assess the immediate impact of the respective exercises on happiness, optimism, and IBS knowledge, 2-tailed paired *t* tests will be used. Between-group differences in the proportion who achieve the MCID (≥50-point reduction in the IBS-SSS) will be evaluated using logistic regression. Achieving the MCID (yes or no) will be modeled as the dependent variable, with treatment group (WISH 2.0 vs educational control) included as the primary independent variable. For clinical outcomes that are measured multiple times per participant, preliminary effects will be explored using mixed-effects regression models with fixed effects for a categorical effect of time and a time-by-treatment interaction with a common baseline for the 2 groups, and an unstructured covariance matrix for the residuals to account for repeated measures. The time-by-treatment interaction terms will estimate the difference between groups in the change over time. Because the mixed-effects model uses maximum likelihood to estimate the coefficients, this approach is valid when missing data are missing at random. Effect sizes (modified Cohen *d*) will be calculated by dividing the group×time coefficient by the SD of the difference estimated using the appropriate variance components from the unstructured covariance matrix. Exploratory mechanistic analyses will use linear mixed models to assess changes in candidate gut-brain mechanisms (eg, HRV, interoception, gene expression, and immune activity) in response to the intervention. If there are skewed distributions in the candidate mechanistic data, logarithmic transformations will be applied. Given the exploratory nature of these analyses, no correction for multiple comparisons will be used. In addition to the models that examine each outcome separately, we will also preliminarily explore whether these gut-brain mechanisms might mediate IBS symptom change using a mediation model. We will calculate the change in the candidate mechanism measurements using linear regression for each participant and the change in the clinical effects outcome measures. Then, we will fit a mediation model with the change in the clinical effects outcome measures as the outcome, the change in the mechanistic measurements as the mediator, and the treatment group as the predictor. The direct and indirect effects of the treatment on the clinical effects outcome measures will be estimated from this approach. Finally, the mediation effects will also be estimated by calculating the change in the treatment effect from the linear mixed model used to assess preliminary clinical effects and the treatment effect from a linear mixed model including treatment, time, time-by-treatment interaction, baseline mechanistic data, and change in mechanistic data as the predictors. The change will show the indirect effect through changes in candidate gut-brain mechanisms. All analyses will be conducted using Stata (version 17). Analyses of clinical and candidate mechanistic outcomes will be conducted on the intention-to-treat population (all randomized participants), with sensitivity analyses using the per-protocol population where appropriate.

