Therefore, informed by the Rome Foundation Consensus Statement on the design of BGBT clinical trials [47], the ORBIT (Obesity-Related Behavioral Intervention Trials) model of behavioral treatment development for chronic diseases [48], and the National Institutes of Health (NIH) stage model for behavioral intervention development [49], and building on prior qualitative research [50] and a systematic review [14], we developed the WISH (Well-being in IBS: Strengths and Happiness) program, a novel, 9-week, manualized, phone-delivered PP intervention specifically adapted to IBS. We examined its feasibility, acceptability, and potential effects on key clinical outcomes in a prior proof-of-concept randomized waitlist-controlled trial (N=22) [35]. WISH was found to be preliminarily feasible (85% of all sessions were completed, exceeding our a priori threshold of 67%), easy to complete (mean 7.2 out of 10, 95% CI 6.70-7.75), and subjectively helpful (mean 7.6 out of 10, 95% CI 7.14-8.01). Promising signals for improvement on several clinically meaningful outcomes, including IBS symptom severity, IBS health-related quality of life, resilience, GI symptom-specific anxiety, restrictive and avoidant eating, perceived stress, and pain catastrophizing, were identified, with effect sizes (Cohen *d*) ranging from 0.1 to 0.7. Of particular note, 61% (11/18) of participants no longer met Rome IV criteria [51] for IBS after intervention completion. Though this proof-of-concept trial provided promising initial data regarding WISH, it had a small sample, no active control condition, no extended follow-up to assess sustainability of effects, and no examination of potential underlying gut-brain mechanisms, the latter of which is often missing from BGBT clinical trials. Additionally, participant feedback highlighted areas for further refinement, including greater customization of intervention content to IBS and expanded descriptions of connections between PP exercises and the gut-brain axis.

Accordingly, we now seek to evaluate the feasibility, acceptability, preliminary effects, and candidate gut-brain mechanisms of an optimized and refined version of WISH (WISH 2.0) in a randomized controlled trial (RCT; N=50) compared with a time- and attention-matched educational control.

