### Randomization and Blinding

At the conclusion of the baseline visit, after providing informed consent and completing all baseline assessments (ie, questionnaires, HRV measurement, and blood sample collection), participants are randomized, stratified by IBS subtype and gender, using the REDCap randomization module to either the PP or educational control program. The randomization sequence was generated by the senior author ([name]) using permuted blocks of variable size, with stratification by IBS subtype (IBS with predominant constipation, IBS with predominant diarrhea, IBS with mixed bowel habits, or unclassified IBS) and gender (male, female, or nonbinary). Allocation concealment is ensured with the REDCap randomization module, which withholds the allocation sequence until after the participant has provided informed consent and completed baseline assessments. After randomization, participants are provided with the appropriate manual. Participants are masked to study hypotheses (ie, whether their randomly assigned program is the intervention or the control), and outcome assessors are masked to treatment assignment.

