#### Exploratory Clinical Outcomes

The comparative effects of the interventions on several health-related, psychological, and health behavior outcomes will be explored at baseline, intervention midpoint, immediately after the intervention, and 3 months after the intervention (ie, extended follow-up). Health-related outcomes include IBS symptom severity (IBS-SSS; primary exploratory clinical outcome) [52], health-related quality of life (IBS Quality of Life Instrument [IBS-QOL] [73]), and IBS diagnosis (Rome IV Diagnostic Questionnaire—IBS Module) [51]. Consistent with the literature [52,74], the MCID for within-participant change from baseline for this trial will be defined a priori as a reduction of ≥50 points in the IBS-SSS total score at the postintervention assessment. Psychological outcomes include positive affect (Positive and Negative Affect Schedule [PANAS] [75]), optimism (Life Orientation Test-Revised [LOT-R] [76] and the Brief State Optimism Measure [B-SOM] [77]), resilience (Brief Resilience Scale [BRS] [78]), self-efficacy (General Self-Efficacy Scale [GSE] [79]), depression and anxiety (Hospital Anxiety and Depression Scale [HADS] [80]), GI symptom-specific anxiety (Visceral Sensitivity Index [VSI] [81]), response to pain (the Pain Catastrophizing Scale [PCS] [66]), and perceived stress (the Perceived Stress Scale (PSS) [82]). Health behavior outcomes include physical activity (International Physical Activity Questionnaire [IPAQ] [83]) and avoidant and restrictive eating (Nine Item Avoidant/Restrictive Food Intake Disorder Screen (NIAS) [84]).

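### The MCID logistic regression, as written, cannot include every randomized participant, and it does not name baseline IBS-SSS

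*Protocol article*

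**What the plan says.** The Hypotheses section (Aim 1) predicts that more WISH 2.0 than control participants will improve by at least 50 IBS-SSS points from baseline. The Exploratory Clinical Outcomes section fixes the time point: "a reduction of ≥50 points in the IBS-SSS total score at the postintervention assessment".

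The Statistical Analysis Plan section compares the proportions by logistic regression: "Achieving the MCID (yes or no) will be modeled as the dependent variable, with treatment group (WISH 2.0 vs educational control") as the primary independent variable. It names no other regressor for this model. It then states the population: analyses of clinical and mechanistic outcomes "will be conducted on the intention-to-treat population (all randomized participants), with sensitivity analyses using the per-protocol population where appropriate".

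Its one statement on missing clinical data is tied to the other model: "Because the mixed-effects model uses maximum likelihood to estimate the coefficients, this approach is valid when missing data are missing at random". That mixed model has categorical time, a time-by-treatment interaction and a baseline common to both groups, so it already uses baseline IBS-SSS.

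The Randomization and Blinding section says that "participants are randomized, stratified by IBS subtype and gender, using the REDCap randomization module". Neither model lists subtype or gender. The Participants section sets no minimum IBS-SSS for entry.

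**The concern.** Two statements in one section do not fit together. The population is everyone randomized, but the model needs a yes/no value that exists only when the postintervention score exists. Without a rule that supplies the value, the model can run only on participants who have that score.

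The missing-at-random sentence does not help here. The mixed model can borrow from the midpoint and 3-month scores of someone who missed the postintervention visit. A single-visit logistic model cannot. With treatment as its only regressor, it needs a stricter condition: within each arm, missingness must be unrelated to response. The two IBS-SSS analyses would then rest on different participants and different assumptions under one intention-to-treat label.

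Baseline is a second, smaller matter. Response is a change from baseline, so the starting score affects the chance of responding. Taking zero as the scale's floor, someone who enters below 50 cannot respond at all. Baseline is collected before randomization, so using it costs nothing.

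At stake is the estimate, not a significance claim. The Discussion says that promising signals will inform a fully powered trial, and this responder contrast is one of those signals.

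**Working it through.** **The plan's own figures.** The article gives no power, dropout rate or responder rate for the MCID comparison, so there is nothing to reproduce for this test. Its nearest figure, 90% power for feasibility (n = 25, 0.80 against 0.50, two-sided 0.05), does reproduce: Φ((0.30·√25 − 1.96·√0.25)/√0.16) = Φ(0.52/0.40) = Φ(1.30) = 0.903. This point does not affect it.

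**Inputs.** From the article: 50 randomized 1:1, so 25 per arm; 4 subtype levels and 3 gender levels. Assumed: response of 40% (control) and 60% (WISH 2.0) among those observed, and missing postintervention scores of 0% to 25%.

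**Effect of the missing-score rule.** Let p be response among those observed and m the fraction missing (C = control, W = WISH 2.0).
- Observed only: RD = pW − pC.
- Missing as non-response: RD = pW(1 − mW) − pC(1 − mC).
- Lower bound: missing WISH all fail and missing control all respond, pW(1 − mW) − [pC(1 − mC) + mC].
- Upper bound: the reverse, pW(1 − mW) + mW − pC(1 − mC).

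| Missing C / W | Observed only | Missing = non-response | Bounds |
|---|---|---|---|
| 0% / 0% | 0.20 | 0.60 − 0.40 = 0.20 | 0.20 to 0.20 |
| 10% / 10% | 0.20 | 0.54 − 0.36 = 0.18 | 0.08 to 0.28 |
| 18% / 18% | 0.20 | 0.492 − 0.328 = 0.164 | −0.016 to 0.344 |
| 10% / 25% | 0.20 | 0.45 − 0.36 = 0.09 | −0.01 to 0.34 |
| 25% / 10% | 0.20 | 0.54 − 0.30 = 0.24 | −0.01 to 0.34 |

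The odds ratio is 2.25 in the observed-only column. Under the non-response rule it is (0.45/0.55)/(0.36/0.64) = 1.45 for 10%/25%, and (0.54/0.46)/(0.30/0.70) = 2.74 for 25%/10%. None of these is the true answer. They show how far the result can move while the rule is open.

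**Effect on power.** With power = Φ((0.20·√n − 1.96·√(2·0.5·0.5))/√(0.24 + 0.24)):
- n = 25 per arm: Φ((1.000 − 1.386)/0.693) = 0.29.
- n = 20.5 per arm (18% missing): Φ((0.906 − 1.386)/0.693) = 0.24.

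**Baseline IBS-SSS in the logistic model.** Simulated trials of 50, all inputs assumed:
- Baseline SD 75, baseline-post slope 0.6, residual SD 70, 40-point effect: 30.5% to 32.9% with no missing scores, and 23.8% to 26.4% with 18% missing. The gain is 2.4 to 2.6 points.
- SD 80, correlation about 0.45, 50-point effect: 32.0% to 35.9%, a gain of 3.9 points.
- SD 80, correlation 0.3 to 0.6, 50-point effect: gains of about 3 to 8 points, with type I error near 5%.

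**Stratification factors in the logistic model.** There are 4 × 3 = 12 strata, and 50/12 is about 4 participants each. In the first simulation setting, assuming 3% nonbinary and 10% unclassified IBS, adding subtype and gender dummies to the baseline-adjusted model gave power of 29.4% (no missing) and 21.9% (18% missing), below the unadjusted 30.5% and 23.8%. Separation or non-convergence occurred in 57% to 64% of runs. Type I error was 4.5% to 5.5% for all models, with or without these factors.

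**The case against.** The article condenses a fuller plan. It never says that participants without a score are removed; that follows from how the model works. Calling treatment the primary independent variable leaves room for covariates, so baseline is unnamed rather than excluded. Missing-data rules and covariate lists often sit in a separate analysis plan. This stands as a limit on wording, and it would dispose of the point if the article were merely silent. But the article commits to a population and to a model that cannot deliver it, and it gives its missing-data justification for the other model alone.

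The comparison is also exploratory, the trial is not powered for it, and IBS-SSS has a mixed model that handles both baseline and missing visits. That stands and limits the weight of the point. So does the fact that stopping sessions is not the same as missing an assessment: assessments are paid separately, and the dropout rule under Primary Outcomes concerns exercises only.

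A reader might infer the size of the problem from the earlier proof-of-concept trial, where "61% (11/18) of participants no longer met Rome IV criteria" although 22 were randomized, and conclude that completer responder rates are inflated. The documents do not support this. That figure is diagnostic status, not a 50-point fall; the article does not explain the denominator of 18; and whether an observed-only contrast is biased depends on why scores are missing.

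A reader might also infer that leaving subtype and gender out of the logistic model is a defect. The simulation shows no inflation of type I error without them, and a fragile fit with them.

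**Conclusion.** The point holds in a limited form. The MCID logistic regression, as stated, cannot include randomized participants who lack a postintervention IBS-SSS, which conflicts with the stated all-randomized analysis. The missing-at-random argument does not reach this model. Baseline IBS-SSS should be named in it.

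The missing-score rule matters more: under assumed response of 40% versus 60% and unequal loss of 10% and 25%, it moves the risk difference from 0.20 to 0.09 or 0.24. With equal loss of 10% the shift is only to 0.18. The gain from baseline adjustment is modest, roughly 2 to 8 power points. All of these sizes rest on assumed dropout, response rates, SDs and correlations, because the article gives none for this endpoint. The primary feasibility and acceptability conclusions are untouched. This should be corrected, but it does not threaten the trial.

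**What to change.** In the Statistical Analysis Plan section:

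1. Multiply impute a missing postintervention IBS-SSS from treatment arm and the baseline, midpoint and 3-month scores. Derive the 50-point response in each imputed set, so that the logistic model covers all randomized participants.
2. Add baseline IBS-SSS as a covariate in that model, and report the risk difference with its 95% CI.
3. As a sensitivity analysis, count missing as non-response.
4. Say that the missing-at-random sentence refers to the mixed model, and state the assumption behind the imputation.
5. Add subtype and gender, with sparse levels collapsed, to the mixed model only. Do not require them in the logistic model at N = 50.

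The cost is a few lines of text, somewhat more analysis code and a prior decision on which categories to collapse. No new data are needed. With 20 of 50 enrolled as of July 2026, the change can still be fixed before the outcome comparison is made.

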### Study Design

This study is a single-site, parallel-group pilot RCT that aims to enroll 50 adults with IBS. Participants are randomized 1:1 to WISH 2.0 or a time- and attention-matched educational control condition. The intervention period is 9 weeks, with extended follow-up at 3 months after the intervention. The trial was prospectively registered at ClinicalTrials.gov (NCT06866106). This protocol is reported in accordance with the SPIRIT (Standard Protocol Items: Recommendations for Interventional Trials) 2025 statement (Checklist 1), the CONSORT (Consolidated Standards of Reporting Trials) 2025 statement [53], and the CONSORT extension for pilot and feasibility trials [54].

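### Maximum likelihood with an unstructured covariance in 50 participants gives slightly narrow intervals for the clinical outcomes if normal limits are used; REML with small-sample degrees of freedom is the better choice

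*Protocol article*

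**What the plan says.** The Study Design section of the protocol article says the trial "aims to enroll 50 adults with IBS", allocated 1:1. Under Exploratory Clinical Outcomes, the effects "will be explored at baseline, intervention midpoint, immediately after the intervention, and 3 months after the intervention", so there are four visits.

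For clinical outcomes measured more than once, the Statistical Analysis Plan section treats time as categorical, lets treatment enter through its interaction with time, and gives both arms one shared baseline mean. The covariance is left free across visits: "an unstructured covariance matrix for the residuals to account for repeated measures". The estimator is named in the sentence on missing data: "Because the mixed-effects model uses maximum likelihood to estimate the coefficients, this approach is valid when missing data are missing at random". The modified Cohen d is obtained by "dividing the group×time coefficient by the SD of the difference estimated using the appropriate variance components from the unstructured covariance matrix".

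The software is Stata 17. The section mentions neither REML nor a degrees-of-freedom method, and it does not say whether tests and intervals use a normal or a t reference. The mechanistic outcomes are to be analysed with linear mixed models, for which no estimator or covariance structure is given.

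**The concern.** ML estimates variances as if the mean parameters were known, so in small samples the variance components come out too small. The standard errors of the treatment contrasts are then too small, and so is the SD that divides the coefficient to give d. If normal limits are used as well, the uncertainty in the estimated covariance is ignored, and the two errors act in the same direction.

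The only reason given for ML is its validity when data are missing at random. REML is also likelihood-based and shares that property, so the reason does not favour full ML.

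At stake is whether the effect sizes and intervals that this pilot hands to a later trial are as precise as they claim to be.

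**Working it through.** 1. **The plan's own figures.** The article gives no interval width, coverage or d for these models, so there is nothing to reproduce on this point. Its arithmetic elsewhere checks out. Feasibility power for 80% against 50% with n = 25 is Φ[(0.30 − 1.96 × 0.10) / 0.08] = Φ(1.30) = 0.903, against the stated 90%.

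2. **Inputs from the article.** N = 50 (25 per arm), four visits, common baseline, categorical time, ML, unstructured covariance.

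3. **Assumptions not in the article.** Correlation between visits 0.4-0.6, dropout 0-30%, true d = 0.40 (a small-to-medium effect), and normal limits under ML.

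4. **Parameter count.** There are 4 time means + 3 time-by-treatment terms = 7 fixed effects, and 4 × 5 / 2 = 10 covariance parameters.

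5. **Closed form, complete data, one post-baseline contrast.** The common-baseline model then reduces to a regression of the outcome on group and baseline, with 3 mean coefficients.
   - ML divides the residual sum of squares by 50 instead of 47. The variance ratio is 47/50 = 0.94, and the SE ratio is √0.94 = 0.970.
   - A normal limit in place of t with 47 df gives 1.96 / 2.01 = 0.974.
   - The width ratio is 0.970 × 0.974 = 0.945, and coverage is about 93.6%.
   - With t limits only the first factor remains, so the narrowing is about 3% instead of about 5.5%.

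6. **Complete-data simulation, 100,000 runs per setting.** This also allows for the estimated baseline slope.

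| N | Coverage, ML with normal limits | Coverage, exact t interval | Width ratio | ML SD of change / true SD |
|---|---|---|---|---|
| 50 | 93.2-93.3% | 94.9% | 0.935 | 0.976-0.977 |
| 40 | 92.9-93.0% | 95.0-95.1% | 0.918 | 0.970-0.972 |

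   The row for 40 is a harsh stand-in for 20% dropout, because it discards all partial data.

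7. **Full four-visit model with 20% dropout, correlation 0.5, 6,400 runs.** ML with normal limits covers 93.1%, so type I error is about 6.9%. REML with t limits (observed n minus 3 df) covers 94.5%. The ML interval is 0.947 times the REML interval. The treatment contrast itself is the same under both to 4 decimals.

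8. **Effect size.** In the same runs mean d is 0.410 under ML and 0.402 under REML, a ratio of 1.020. Across all settings the ratio runs from 1.017 to 1.021. REML does not remove all bias in d: about 1-2% remains from dividing by an estimated SD.

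**The case against.** The strongest reply is that this is a software setting which an article may leave to the full analysis plan, and that the ML clause is there only to support the missing-at-random claim. The phrase may also be shorthand for likelihood-based estimation in general, REML included. The interval result further depends on normal limits that the article never states.

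Part of this stands. The reference distribution is an assumption, and if REML was meant, one word settles the matter. But the article does name ML, fixes the covariance structure and takes the denominator of d from it, so this is a stated choice that can be improved and not a mere gap.

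The reply is also right about scale. With 25 per arm the sampling SE of d is roughly √(2/25) = 0.28, and the difference of 0.008 between ML and REML is about 3% of that.

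A reader might infer that every between-group result is affected. The documents do not support this. The ML and unstructured-covariance wording covers only the clinical outcomes measured repeatedly. The MCID comparison is a logistic regression, and feasibility uses exact binomial intervals. HRV, transcriptome and serum markers are measured at two visits, where an unstructured matrix has 3 parameters, not 10.

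A reader might also infer that the excess false positives, with no multiplicity correction, decide which signals go forward. No section says that signals are chosen by p < 0.05. The Power and Sample Size section says the trial is not designed to find significant group differences in these outcomes.

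**Conclusion.** The point holds as a minor one, for the exploratory clinical outcomes analysed by the repeated-measures model. With normal limits, 95% intervals are about 5-6% too narrow, coverage is about 93% and type I error is about 6.5-7%. The modified d is about 2% above its REML value. These sizes rest on assumed correlations of 0.4-0.6, dropout of 0-30% and a normal reference; t limits would roughly halve the interval effect. The mechanistic models share the problem only if they are fitted in the same way.

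The missing-at-random sentence should not be read as an error: it is correct, and it applies equally to REML. The remedy should not be read as complete or free either. The check used a simple t reference as a stand-in for Kenward-Roger or Satterthwaite, and coverage with dropout came back to about 94.5%, not exactly 95%.

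**What to change.** State that the mixed models for the repeatedly measured clinical outcomes are fitted by REML with Kenward-Roger or Satterthwaite degrees of freedom, and that the SD for the modified d comes from the REML covariance matrix. Keep the missing-at-random statement, reworded to refer to likelihood-based estimation. If the mechanistic mixed models are to be fitted the same way, say so there too.

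The cost is a sentence in the plan and a change of estimation options. Treatment contrasts are essentially unchanged. Compared with ML and normal limits, intervals widen by about 5-6% (1 / 0.945 = 1.058), and a small bias in d remains. With 20 participants enrolled by July 2026 and completion expected in August 2028, the change can be made before the final analysis.

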#### Aim 2: Candidate Gut-Brain Mechanisms

We hypothesize that participation in WISH 2.0 will be associated with changes in at least one of the following candidate gut-brain mechanisms: autonomic function (heart rate variability [HRV]), interoception (self-report measure), stress-related gene expression (whole transcriptome RNA sequencing), and immune system activation (serum inflammatory biomarkers). We further hypothesize that any changes in these candidate mechanisms will be associated with reductions in IBS symptom severity over time.

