#### Exploratory Mechanistic Outcomes

Exploratory mechanistic outcomes include autonomic function (as measured by HRV frequency-domain variable measures, specifically low-frequency power, high-frequency power, and the low-frequency/high-frequency ratio [85,86], using the HeartMath Institute emWave Pro Plus), self-reported interoception (Multidimensional Assessment of Interoceptive Awareness Version 2 [MAIA-2] [87]), stress-mediated gene expression (whole transcriptome analysis of blood by RNA sequencing), and immune system activation (serum inflammatory biomarker levels, such as interleukin-6, tumor necrosis factor-α, and C-reactive protein). Each of these 4 candidate gut-brain mechanisms is known to contribute to IBS pathophysiology (at least in subsets of patients) [88-99] and has established associations with PP well-being [100-104]; thus, each holds promise as a potential mechanism linking PP well-being and IBS symptom severity. These exploratory mechanisms will largely be assessed before and immediately after the intervention, except for interoception, as this is measured by a questionnaire that can be completed remotely at the intervention midpoint and extended follow-up.

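### The no-correction rule covers whole-transcriptome gene expression, so gene-by-gene testing would meet the first part of the Aim 2 hypothesis by chance

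*Protocol article*

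**What the plan says.** Aim 2 in the Hypotheses section has two parts. The first is that "participation in WISH 2.0 will be associated with changes in at least one of the following candidate gut-brain mechanisms". The four mechanisms are autonomic function, interoception, stress-related gene expression and immune activation. The second part is that "any changes in these candidate mechanisms will be associated with reductions in IBS symptom severity over time".

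The Exploratory Mechanistic Outcomes section gives the measures:
- **Heart rate variability:** "specifically low-frequency power, high-frequency power, and the low-frequency/high-frequency ratio".
- **Interoception:** the MAIA-2 questionnaire.
- **Immune activation:** an open list of serum markers, with three given as examples (interleukin-6, tumor necrosis factor-α, C-reactive protein).
- **Gene expression:** "whole transcriptome analysis of blood by RNA sequencing". No gene set, pathway or composite score is named.

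The Statistical Analysis Plan section then specifies "linear mixed models to assess changes in candidate gut-brain mechanisms (eg, HRV, interoception, gene expression, and immune activity) in response to the intervention". It states "Given the exploratory nature of these analyses, no correction for multiple comparisons will be used", and introduces the mediation work with "In addition to the models that examine each outcome separately". The Power and Sample Size section and the Discussion both say that the mechanistic analyses are exploratory and not powered.

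**The concern.** Leaving a handful of named markers uncorrected in a disclosed exploratory pilot is defensible. A transcriptome-wide screen is different in scale. Here the article does more than stay silent: it rules correction out, for a group of analyses in which gene expression is named. A later analysis plan that applied false discovery rate control would contradict it.

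Aim 2 also has an at-least-one rule, so its chance of being met with no true effect grows with every measure tested. What is at stake is the secondary aim. The article says the mechanistic results may help to pick candidates for a larger efficacy trial. A gene list made up largely of chance hits cannot support that choice.

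**Working it through.** **The plan's own figure.** The only number given for Aim 2 is 81% power for mediation, with n = 50, effect 0.44, mediator SD 1, treatment-mediator correlation 0.4 and two-sided .05. With residual SD taken as 1:

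- 0.44 × √(50 × (1 − 0.4²)) = 0.44 × √42 = 2.85
- power = Φ(2.85 − 1.96) = 0.814, which agrees with the stated 81%.

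That figure is for a single mediator at .05. The article states no error rate for the at-least-one hypothesis.

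**Inputs for the check.**
- Named non-transcriptomic measures: 3 heart rate variability + 1 MAIA-2 + 3 serum markers = 7. This is a low count, because the marker list is open and the number of MAIA-2 scores analysed is not stated.
- Number of genes tested: not stated. Assumed range: from one score to 20,000 genes.
- Per-test threshold: assumed to be .05 two-sided. The article uses that level in its power calculations but states none for the mechanistic models.

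**Formulas, with no true effect on any measure.** For k independent tests, P(at least one p < .05) = 1 − 0.95^k. The expected number of false positives is 0.05 × k, whatever the correlation.

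| Tests | k | P(at least one) | Expected false positives |
|---|---|---|---|
| One per mechanism | 4 | 0.185 | 0.2 |
| Named measures, no genes | 7 | 0.302 | 0.35 |
| Named measures + one expression score | 8 | 0.337 | 0.4 |
| Any 59 tests | 59 | 0.952 | 2.95 |
| Gene by gene, low | 12,000 | about 1 | 600 |
| Gene by gene, high | 20,000 | about 1 | 1,000 |

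**Correlation.** The measures are not independent; the low/high-frequency ratio, for example, is a function of the other two.
- *Eight tests.* Simulation with within-mechanism correlation of 0.3 to 0.8 gives 0.33 down to 0.27.
- *Genes.* With 10,000 or 20,000 genes in strongly correlated blocks, the chance of at least one hit stayed at 0.99 to 1.00. It fell clearly (to 0.75 and 0.47) only with 1,000 genes in two blocks of 500, a far smaller screen than a whole transcriptome.

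**The second part of Aim 2.** Suppose association with symptom reduction were also tested gene by gene at .05, and that this test were independent of the first under no effect. Then 0.05 × 600 = 30 to 0.05 × 1,000 = 50 genes would be expected to pass both tests by chance. This rests on a further assumption, because the article does not say that the association will be tested this way.

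**The case against.** Gene-by-gene testing is inferred; the article does not state it. It names the construct as stress-related gene expression and gives sequencing as the assay. It describes mechanistic measurements that enter a mixed model and then a mediation model, which suits one or a few scores at least as well as thousands of separate fits. Reducing sequence data to an analysis variable is often left to a full analysis plan. No significance rule is given for what counts as a change. The work is openly exploratory and unpowered, and no primary conclusion depends on it.

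Most of this stands, and it limits the size of the point. A reader might infer that Aim 2 as a whole cannot fail, or that it will certainly be met by chance. The documents do not support that. Near-certainty needs single-gene testing at a nominal threshold, and it applies to the first part only. The count of 600 to 1,000 also assumes no effect on any gene, so it does not show what share of a real gene list would be false.

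The objection does not remove the sentence that rules out correction. As written, that sentence covers gene expression, and nothing else in the article limits the transcriptome to a score. The exploratory label does not help either, because the results are meant to guide the choice of mechanisms for the next trial.

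**Conclusion.** The concern holds in a limited form. Taken literally, the no-correction rule applies to a whole-transcriptome outcome with no named gene set or score. If genes are tested singly at .05, about 600 to 1,000 false positives are expected under no effect (assuming 12,000 to 20,000 genes), and the first part of Aim 2 is met almost surely. If one expression score is used, the chance is about 19% (one test per mechanism) to 34% (eight tests) under independence. That is inflated but not certain, and it is tolerable for a short exploratory list that is disclosed as such. The second part of Aim 2 is not met automatically. Feasibility and acceptability are unaffected. The wording should be fixed, but it is no threat to the trial's primary conclusions.

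**What to change.** 1. Limit the no-correction sentence to the short list of named non-transcriptomic measures.
2. For the transcriptome, do one of two things: control the false discovery rate across genes (Benjamini-Hochberg, for example at 5% or 10%), or prespecify one stress-related gene-set score as the endpoint.
3. State that uncorrected single-gene p-values do not count towards the at-least-one-mechanism hypothesis.

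With seven uncorrected measures and the transcriptome held to a 5% chance of any false hit under no effect, the chance of at least one nominal result is 1 − 0.95^8 = 0.337. At 10% for the transcriptome it is 1 − 0.95^7 × 0.90 = 0.372. The at-least-one result should therefore still be reported as hypothesis-generating. A Holm adjustment across the four mechanisms would bring it to about 5%, but that is optional in a pilot of this size and is not asked for here.

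The cost is a few sentences and routine code, with no change to data collection or sample size. The downside is fewer nominally significant genes. The article reports 20 of 50 participants enrolled as of July 2026 and completion in August 2028, so there is time to settle this before the mechanistic results are analysed.
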